**Methods:**

This study will be conducted in two phases. In phase 1, nutrition fact labels and traffic light labels will be assessed through focus group discussions and interviews among different groups of mothers, industrialists and nutrition and food industry specialists as to determine strengths and weaknesses of the current labels on packaged products. Then, the initial layout of the physical activity calorie equivalent label will be drawn with respect to the viewpoints received from mothers. Thereafter, we will include the scientific opinions to it for creating the first draft of our new label. In phase 2, a total of 500 mothers of students 6–12 years old randomly assigned to five groups. The study groups will be as follows: (1) without nutrition label group, (2) current traffic light label group, (3) current traffic light label group in which, a brochure will be used to inform mothers, (4) physical activity calorie equivalent label group, and (5) physical activity calorie equivalent label group in which a brochure will be used to inform mothers. Some samples of dairy products, beverages, cakes, and biscuits will be presented. ANOVA and multiple linear regressions will be used to examine the association between the label type and the main consequence (energy of the selected products) and secondary outcome (time).

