Products included in the “without nutrition label” group will provide no nutrition information. There will be no change in the traffic light label group and the labels will appear exactly as produced by factories. Calories and serving sizes of products on labels will be based on factories definition and we do not change them. Each particular food with either no label, or old traffic light label, or our newly designed label will be presented into 3 classrooms similarly. Groups in traffic light label and physical activity calorie equivalent label will only be different in the form of figures and presentation of some information such as physical activity. Finally, the products with physical activity calorie equivalent labels will be covered with the new designed label. Each mother will be asked to imagine she is in a supermarket, choose one product that she wants from each category to buy for her family; place them in a bag inside the room, and then leave there. One of the researchers will record food items. For example, one package of creamy cake has about 320 cal, while there is another cake with only 130 cal; so we expect mothers to choose better option based on the information provided by the labels. Thus, at the end of the study, the total calories from each category as well as the total calories of all selected foods will be compared among different 5 groups. For each of the five groups, the “time” spent by each participant while selecting food items will be recorded by the researcher. After the food choice stage, a series of short questions will be asked in order to assess the mothers’ attention to the mentioned labels. All the collected data will be entered into a database.

Accordingly, the major consequence obtained in this step will show the effect of the new designed label that focuses on the differences in calories for each food group. Accordingly, the major consequence obtains from this step would be the effect of the new label on choosing lower calories goods by consumers and the second outcome would be the time spent while food selection according to different labels.

#### Randomization method in phase 2

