#### Method of calculating sample size and number

We calculated the number of participants by using G*Power software 3.1 [28]. In this regard power analysis was applied based on a linear multiple regressions with an assumed small to medium effect size (f = 0.18). The total sample size in this case will be 481 with power of 0.9. The sample size is 96 in each arm after attrition, and we scaled that up to *n* = 100 therefore, 500 subjects will be studied in total. Due to the multiple comparisons, alpha level will be adjusted and interpretation of statistically significant results will be done by taking conservative cautions.

#### Qualitative analysis of data in phase 1

The MAXQDA 10 software will be used to analyze the interviews. This software is used to analyze social-oriented texts [29]. Qualitative analysis with thematic approach will be used. It will be done as follow. First, data will be analyzed after each group discussion or interview; for this purpose, all the data will be entered into the software in a textual format. The strengths, weaknesses, description, and information for the new physical activity calorie equivalent label will be defined as categories, and each category will be stored in a special part of the software. Thereafter, decision will be made on coding units after reading the text for several times and the codes will be added to each relevant category at the same page of the software. At this point, classification will be done using the data of the study, and the stability of the coding will be tested. The coding stability will be re-checked after encoding the full text in the software. Finally, the structures of meanings will be provided based on the data inference.

#### Statistical analysis of data in phase 2

Analysis of Variance (ANOVA) will be used to examine the relationship between the label type and the main consequence showing calorie of the selected products and the second outcome which is spent time during food selection. The purpose of this analysis is to see whether the difference between different groups has a significant effect on the main outcome. In order to adjust the effect of confounders (education level, body mass index, age, and socioeconomic status) multiple linear regressions will be used and the energy of the selected food products in each group will be analyzed. In all tests, type I error will be considered 5% and the data will be analyzed using the Stata 12 and SPSS version 16.

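### The abstract lists regression for both energy and selection time, but the analysis section names only energy for the covariate-adjusted model, so time is left with an unadjusted ANOVA and may forgo some precision

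*Protocol article*

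**What the plan says.** In the protocol article's abstract (Methods), one sentence covers both outcomes: "ANOVA and multiple linear regressions will be used to examine the association between the label type and the main consequence". It gives the outcomes as "the main consequence (energy of the selected products) and secondary outcome (time". No covariates are mentioned there. The Phase 2: intervention section confirms the secondary outcome: "the second outcome would be the time spent while food selection according to different labels".

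The section headed Statistical analysis of data in phase 2 is more specific. ANOVA is assigned to calories and also to "the second outcome which is spent time during food selection". The regression then comes with its purpose and covariates: "In order to adjust the effect of confounders (education level, body mass index, age, and socioeconomic status) multiple linear regressions will be used". The outcome named for it is energy: "multiple linear regressions will be used and the energy of the selected food products in each group will be analyzed". Time is not mentioned again.

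**The concern.** The two places do not give the same plan for the secondary outcome. A reader of the abstract expects a regression result for time. A reader of the analysis section expects an ANOVA only.

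Two things are at stake, both modest.

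- **Prespecification.** If it is unclear whether an adjusted analysis of time belongs to the plan, the adjusted or the unadjusted result could be favoured once the data are seen.
- **Precision.** Each mother chooses from at least 70 products (at least 30 dairy, 20 beverages, 20 cakes and biscuits). Mothers must be literate, but there is no age limit and education may vary widely. Age and education could plausibly predict how long she takes. Any such variation stays in the error term of an unadjusted ANOVA, although the energy model already requires the covariates that could remove it.

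**Working it through.** **Inputs from the protocol article.** Five groups of 100, N = 500. Effect size f = 0.18, so f² = 0.0324. Stated requirement of 481 at power 0.9. Type I error 5%. Four named covariates.

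**Inputs assumed.** R², the share of the within-group variance of selection time explained by the four covariates, is not given, so I use 0 to 0.30. No effect size for time is given either; for illustration I let f = 0.18 apply to it.

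**Step 1, the plan's own figure.** I use the noncentral F test with numerator df 4 and noncentrality λ = N·f². At N = 481, λ = 481 × 0.0324 = 15.58.

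- Five-group ANOVA (denominator df 476): power 0.9005. At N = 480 power is 0.8998, so 481 is the smallest N that reaches 0.90.
- Regression with 4 tested predictors out of 8 (four group indicators plus four covariates; denominator df 472): power 0.9005, again N = 481.

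The stated 481 reproduces with or without the covariates, so the sample size does not depend on this point.

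**Step 2, unadjusted analysis of time at N = 500.** λ = 500 × 0.0324 = 16.2, denominator df 495, power 0.913.

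**Step 3, adjusted analysis of time at N = 500.** Four covariates take the denominator df from 495 to 491.

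- SE ratio, adjusted to unadjusted = √[(1 − R²) × 495/491]
- λ = 16.2/(1 − R²)

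| Assumed R² | SE ratio | Change in SE | λ | Power |
|---|---|---|---|---|
| 0 | 1.004 | +0.4% | 16.20 | 0.913 |
| 0.01 | 0.999 | −0.1% | 16.36 | 0.916 |
| 0.05 | 0.979 | −2.1% | 17.05 | 0.927 |
| 0.10 | 0.953 | −4.7% | 18.00 | 0.941 |
| 0.20 | 0.898 | −10.2% | 20.25 | 0.965 |
| 0.30 | 0.840 | −16.0% | 23.14 | 0.982 |

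**Step 4, break-even.** The SE falls once (1 − R²) × 495/491 < 1, that is R² > 4/495 = 0.8%.

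**The case against.** The strongest reply is that nothing invalid is planned. Groups are randomised within schools, so omitting these covariates does not bias the comparison of time, and ANOVA is an acceptable analysis of a secondary outcome. The article gives confounder adjustment, not precision, as the purpose of the regression. The abstract can also be read as a compressed summary in which the two methods and two outcomes are listed without every pairing being intended. A condensed article may leave such detail to a fuller document.

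Most of this stands, and it rules out several stronger readings that a reader might infer.

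- That the abstract promises covariate adjustment for both outcomes. It names regression but no covariates; those appear only in the analysis section.
- That the analysis section restricts regression to energy. It names energy and is silent on time, with no word of exclusion. That time stays unadjusted is the natural reading, but an inference.
- That the time comparison is biased or unreliable. Randomisation answers this.
- That precision is certainly lost, or that adjustment is free. No R² for time is given, the gain could be nil, and four degrees of freedom are spent. The Phase 2: intervention section mentions only demographic data without listing items. That the four covariates will be available follows from the energy model needing them.

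What the reply does not remove is the mismatch itself. The article states methods for time in two places and they differ. That is a matter of what the document says, not of detail left out.

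**Conclusion.** The point holds as a small inconsistency on a secondary outcome, with a possible precision gain attached. Under an assumed R² of 0 to 30%, adjusting time would change its standard error by +0.4% to −16%. If f = 0.18 applied to time, power would go from 0.913 to between 0.913 and 0.982, a gain of at most about 7 percentage points (0.982 − 0.913 = 0.069). Both the R² range and the use of f = 0.18 for time are assumptions. The unadjusted comparison remains valid, and neither the primary analysis nor the figure of 481 is affected. This is an improvement worth making, not a defect that threatens the trial.

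**What to change.** In Statistical analysis of data in phase 2, add one sentence: selection time is also analysed with the same prespecified linear regression as energy (group indicators plus education level, body mass index, age and socioeconomic status), and this result is reported alongside the ANOVA. Then align the abstract's methods sentence with that section, so that both state which methods apply to which outcome.

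The cost is one sentence, one more model and four degrees of freedom (0.4% on the standard error if the covariates explain nothing). No data are needed beyond what the energy model already requires.

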### Ethical considerations

This study is approved by Tehran University of Medical Sciences (96–03–161-37,037). It has also been registered in the Iranian Registry of Clinical Trials (IRCT20181002041201N1).

In the qualitative section, the participants will be informed of the study objectives.

Before conducting the interviews, the interviewees will be briefed of the purpose of the research and participants will be assured that the information would be used only for research purposes and would not be accessible for others who are not in the research team. In addition, no sensitive date will be requested and hence, no such data will be provided. The information of all participants will remain confidential and caution will be made to avoid referring to the names or terms that could reveal the identity of the individual while implementing the interviews. First author will take consent letter from participants and they will exclude from the study whenever they wish to.

Mothers with 18.5 > BMI > =25 and children with − 1 < height Z-score < + 1 and/or − 1 < BMI Z-score < + 1 will be considered as under and/or over-nourish and will be provided with free counseling and training by a registered dietitian if they wish to.

In the quantitative phase, the participants will be asked to choose from different food groups while they are unaware of the purpose of the study. In similar studies, to examine the actual effect of the intervention, the participants are not informed about the reason for the intervention [30, 31] and they are unaware of the main purpose. In addition, the participants’ information will remain confidential and their contribution will be acknowledged.

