### Selection criteria

Participants will be literate mothers who are willing to participate in the study. The mothers who are nutritionist or food technologist will not be included.The age of students will be 6–12 years. However, we will put no limitation for age of mothers who will enroll the study.

### Phase 1

FGDs will consist of 6 to 10 people and at least 6 industrialists and experts will be interview, and will continue until data saturation is achieved.

### Phase 2

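### The printed cut-offs for under- or over-nourished participants contradict their label: no mother can meet them, and for children they pick out the middle of the distribution

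*Protocol article*

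**What the plan says.** The rule is a single sentence in the protocol article, under Ethical considerations.

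- **Mothers:** "Mothers with 18.5 > BMI > =25 and children with" gives the BMI condition as one chained inequality.
- **Children:** the two conditions are "1 < height Z-score < + 1" and "1 < BMI Z-score < + 1", each printed with a minus sign before the first 1 and joined by and/or.
- **Label:** those who meet the conditions "will be considered as under and/or over-nourish".
- **Consequence:** they "will be provided with free counseling and training by a registered dietitian if they wish to".

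No other section restates or corrects these cut-offs. Selection criteria asks only that "Participants will be literate mothers who are willing to participate in the study", apart from excluding nutritionists and food technologists and fixing the age of the students. Body mass index returns once, under Statistical analysis of data in phase 2, in the list of "confounders (education level, body mass index, age, and socioeconomic status"; no cut-offs are attached to it there.

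**The concern.** The conditions and the label in this sentence cannot both be right. The mothers' signs point outward, as a rule for two tails needs, but they are chained, so both halves must hold together. The children's signs point inward and describe the central band, yet the children in that band are the ones labelled malnourished.

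What is at stake is a benefit promised to participants. Followed to the letter, the rule offers counselling to no mother, offers it to children close to the reference median, and withholds it from children outside the band on both indices. The children's half is the likelier to cause a practical error: it is a valid, non-empty condition that could be copied into a form or spreadsheet without raising any warning.

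**Working it through.** **Inputs.** From Ethical considerations: BMI cut-offs 18.5 and 25 for mothers; Z-score cut-offs -1 and +1 for children, on height and on BMI. The article gives no resulting count or percentage, so there is no stated figure to reproduce.

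**Mothers.** The chain 18.5 > BMI >= 25 means BMI < 18.5 and BMI >= 25. Any value of 25 or more exceeds 18.5, so the set is empty. A check on BMI values from 10 to 60 in steps of 0.1 found 0 of 501 meeting it. With *or* in place of the chain, 436 of the 501 grid values qualify. That is a count of grid points and says nothing about the share of mothers.

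**Children, logic.** Take the ordinary inclusive reading of and/or (at least one index meets the condition).

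| Child's position | Printed rule | Tail rule, same cut-offs |
|---|---|---|
| Inside the band on both indices | selected | not selected |
| Inside on one, outside on the other | selected | selected |
| Outside the band on both | not selected | selected |

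A child with Z = 0 on both indices is therefore classed as malnourished, and a child at -3 on both is not.

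**Children, size (illustrative).** The documents give neither a Z-score distribution nor a number of children. Assume that the two Z-scores are standard bivariate normal with correlation r.

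- One index: p = P(-1 < Z < 1) = 0.6827, and 1 - p = 0.3173.
- At r = 0:
  - printed rule: 1 - (1 - 0.6827)² = 0.899
  - outside on both, passed over: 0.3173² = 0.101
  - tail rule: 1 - 0.6827² = 0.534
- At r = 1 the indices coincide: printed rule 0.683, passed over 0.317, tail rule 0.317.

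| r | Printed rule selects | Passed over (outside on both) | Tail rule selects |
|---|---|---|---|
| 0 | 89.9% | 10.1% | 53.4% |
| 0.5 | 86.7% | 13.3% | 50.2% |
| 1 | 68.3% | 31.7% | 31.7% |

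The band is symmetric about zero, so negative correlations give the same values.

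If and/or were read strictly as *and*, the printed rule would select children inside the band on both indices. That is 1 minus the last column: 46.6% at r = 0, 49.8% at r = 0.5 and 68.3% at r = 1. The shares change, but on this reading too the rule selects the centre.

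**The case against.** The strongest reply is that this is a slip of notation whose meaning the sentence itself supplies. The label and the referral to a dietitian make the intent plain. For mothers, each half of the chain is correct alone and only the word *or* is missing. Staff cannot act on an empty set, and a dietitian is unlikely to counsel a child near the median as malnourished. The rule has no part in the trial's inference, and the percentages rest on a distribution that the documents do not give.

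Most of this stands, and it is why the point is minor. The mothers' half is the lesser slip; the children's half is a real reversal of signs. The percentages only illustrate, and the contradiction does not depend on them. But an intent that can be inferred does not make the printed rule correct, and the children's version can be applied as written. A typesetting or text-conversion fault cannot be wholly excluded, but it is unlikely: it would have to reverse two separate criteria in the same way and also drop a word from a third. Nor is this a detail left to a fuller document, because the article chose to print the cut-offs.

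One further point has weight. Turning the children's signs round at the printed cut-offs would flag any child with a height Z-score above +1, including a tall child of ordinary BMI. The intended cut-offs therefore need confirming.

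**Conclusion.** The concern holds, as a minor one. The mothers' condition is empty, and the children's condition selects the central band in place of the tails. Both conclusions follow from the printed inequalities alone.

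The shares for children rest on two assumptions: standard bivariate normal Z-scores and the inclusive reading of and/or. The number of children actually affected cannot be worked out from the article. The consequence reaches only an optional offer of counselling; nothing in selection, allocation, the outcomes, the sample size or the planned analysis changes.

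**What to change.** Replace the sentence with a rule of this form: mothers with BMI < 18.5 or BMI >= 25, and children with a height Z-score and/or a BMI Z-score below -1 or above +1, will be considered under- or over-nourished.

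Before it is issued, the investigator should confirm that these cut-offs are the intended ones, in particular whether a height Z-score above +1 alone should trigger the offer. Any working form used to make the offer should be checked against the corrected rule.

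The cost is one corrected sentence and that check, with no change to design, sample size or analysis.

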### Limitations

The final stage of the study will be simulating the environment since the mothers are actually in the sample food selection room, which is one of the study limitations. However, for the purpose of examining the effect of labels, there will be a comparison group and since the conditions are the same for all groups, it will largely moderate the conditions. Furthermore, the mothers will be blinded to the main goal of intervention.

Another limitation is assigning the selection process only to mothers and not involving fathers in the study, so that gender differences will not be clear. The reason for targeting the mothers is that they are more involved in purchasing and preparing food and in different studies [32, 33] it has been founded that women use food labels more than men. Due to Iranian previous studies [34, 35] the use of nutrition labels among people was rare. Thus, we decided to consider women who might be more responsible for preparing foods in households.

In the present study health literacy or nutrition knowledge will not be measured whilst nutritionist or food technologist mothers will not enter in our study. Previous studies in Iran did not report any significant variances of knowledge or usage of nutrition labels [34–36].

## Discussion

Physical activity calorie equivalent labeling is in the testing phase and since this type of labels focuses on the amount of energy received, it can encourage individuals to choose low calorie foods [31]. However, such studies in the real world are scarce [30, 31, 37] and have been mostly done in high-income countries [24, 25, 31, 38, 39]. A combination of training and physical activity calorie equivalent labels can be an effective intervention [29].

A recent systematic review and meta-analysis compared the effect of calorie labeling and physical activity calorie equivalent labeling on calorie ordering of foods in restaurants. The results of this study showed no significant difference in the amount of calories ordered between these two types of labels, although the amount of calories ordered in real condition studies were 65 cal lower than studies in unreal conditions [40].

To the best of the authors’ knowledge, this is the first comparison of physical activity calorie equivalent labels with traffic light labels. The results of this study can be used by policy-makers in three scenarios: 1- collecting comprehensive views of mothers as household representatives, industrialists as executive representatives, and nutritionists and food industry experts as scientific representatives about the existing labels, 2- modifying the current labels according to the results of this study, 3. presenting a new label that meets the needs of consumers.

